## Description of the intervention

*DESIGN*: Considering the objectives of the study, each participant in the sample will carry out, in a randomized sequence, three exercise sessions and one control session. The exercise session will consist of completing the same volume of work (repetitions x kilograms) in leg press, bench press, leg curl, and lat pulldown exercises, but responding to different structures regarding the set configuration. Thus, with a load of 12 maximum repetitions (12RM), an equivalent volume will be completed in each exercise, consisting of 3 sets of 12 repetitions in each exercise, varying the effort structure in each of the sessions: a session with 9 sets of 4 repetitions (4S), corresponding to 33% of effort intensity (4 out of 12 possible repetitions); a session with 6 sets of 6 repetitions (6S), corresponding to 50% effort intensity (6 out of 12 possible repetitions); and finally, a session with 4 sets of 9 repetitions (9S), corresponding to 75% effort intensity. To ensure an equivalent work/rest ratio between sessions, the recovery between sets will be 45, 72, and 120 seconds for 4S, 6S, and 9S, respectively. The rest between exercises will be 4 minutes for all sessions. This procedure ensures equality between sessions in terms of volume, load intensity, recovery time, and session duration, with the independent variable being the set configuration, i.e., the required effort intensity. Additionally, a control session (CON) will be conducted without exercise to provide a baseline reference for the hemodynamic and metabolic behavior of the sample over time. The structure for recording will be the same in 4S, 6S, and 9S: **i)** initial recording for 15 minutes at rest of hemodynamic, metabolic (resting oxygen consumption), indicators of cardiac autonomic modulation, cardiac performance, and measurement of arterial stiffness; **ii)** 10-minute warm-up phase; **iii)** neuromuscular assessment to control fatigue; **iv)** baseline lactate measurement; **v)** completion of the session with an approximate duration of 45 minutes; **vi)** post-exercise lactate measurement; **vii)** neuromuscular measurement after exercise; **viii)** measurement of arterial stiffness; **ix)** repetition of hemodynamic, metabolic, and cardiac autonomic modulation recording at rest for 60 minutes to assess the hypotensive effect of exercise; and **x)** final measurement of arterial stiffness. CON will consist of repeating the aforementioned structure, replacing the exercise routine with 45 minutes of rest. This phase of the project will be carried out in the facilities of the Faculty of Sport Sciences and Physical Education of the University of A Coruña.

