
*PROCEDURES:* Each subject will undergo a total of 8 assessment sessions: **Session 1**: Medical consultation ([name]) to evaluate health status, potential cardiovascular risk factors, contraindications (absolute and relative), and inclusion/exclusion criteria. This consultation will include medical history (including provided previous medical reports), comprehensive physical examination, and complementary tests (with prior informed consent): resting electrocardiogram (ECG), resting spirometry, and ergospirometry with ECG, gas, and BP monitoring. **Session 2**: Anthropometric measurements (weight, height, body mass index, body composition by bioimpedance, skinfold and diameter measurements), bone mineral density using an ultrasound bone densitometer (Sonost 3000, Osteosys Corp., Korea), and familiarization with exercise performance. Exercises have been selected according to international recommendations regarding the use of multi-joint exercises involving large muscle groups. **Sessions 3 and 4**. Dedicated to determining, for each exercise, the load at which the subject can perform a maximum of 12 repetitions (12RM). During the procedure, execution speed will be recorded using the T-Force device to guide load adjustments based on loss of propulsive speed. The procedure will be conducted twice to determine the replicability of the results. A difference of more than 10% between the defined 12RM loads in each session will require a third assessment. Sessions will be separated by at least 72 hours of recovery. **Sessions 5-8**. Correspond to the randomized completion of the 4S, 6S, 9S, and CON sessions. The steps for each session are as follows: Once the subject arrives at the laboratory, they will be prepared for recording using the Task Force Monitor device (CNSystems, Graz, Austria) for ECG, beat-to-beat BP, and impedance cardiography. Additionally, indirect measurement of resting metabolic rate (oxygen consumption) will be conducted using the MetaMax 3B-R2 analyzer (Cortex, Leipzig, Germany). After calibrations, the recording will begin, with the subject lying supine on a stretcher in silence for 15 minutes. Afterward, arterial stiffness will be assessed using the finger-toe pulse wave velocity measurement technique. Next, the warm-up phase will start, consisting of 5 minutes of cycling on an ergometer at a moderate intensity (50-70% of their estimated maximum HR), 2 minutes of joint mobility, and performing 10 repetitions of each exercise at 70% of the load to be used in the session at a moderate execution speed. After 2 minutes of recovery, baseline lactate will be recorded, and the speed of movement for each exercise will be recorded using the T-Force transducer with a load equivalent to 70% of 12RM. This assessment will be used as an indicator of muscle fatigue. The exercise session will then begin, following the previously described guidelines. During this phase, in addition to measuring cardiovascular parameters, mechanical performance in each repetition will be recorded using the T-Force device, as well as perceived exertion at the end of each set using the OMNI-RES scale. One minute after completing the last repetition of the session, a new lactate measurement will be taken, the subject will be instructed to lie back on the stretcher, arterial stiffness will be measured, and cardiovascular recording will be prepared using the Task-Force Monitor device. A post-exercise assessment will then be conducted under the same conditions as the pretest but extended for 60 minutes to contrast recovery and post-exercise reactivation processes. After this measurement, a final assessment of arterial stiffness will be performed. As mentioned earlier, the CON session will have the same content as the experimental sessions, although warm-up processes, neuromuscular fatigue indicators, and exercise performance will not be conducted. All measurements will be taken with participants in a postprandial state (3 hours after the last meal), and they will be asked to avoid caffeine intake on the day of measurement and intense physical activity in the 24 hours preceding measurement. Participants will be asked to maintain their hydration habits in the hours leading up to exercise, although fluid intake will not be allowed during exercise as it may affect some results, such as lactate levels. It should be noted that for this phase of the project, the group has all the necessary equipment except for the horizontal leg press and the pulse wave velocity meter (pOpmetre; Axelife. Saint Nicolas de Redon, France) required to estimate arterial stiffness. Therefore, the budget includes these two pieces of equipment, as well as the cost of consumables for the available equipment.

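### The two descriptions of the control session conflict, and taken together they leave it nominally about 12 minutes shorter between recordings than the exercise sessions

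*Protocol*

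**What the plan says.** Both descriptions are in the Protocol, Description of the intervention.

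- **DESIGN paragraph.** The exercise sessions follow steps i to x. The "10-minute warm-up phase" (step ii), the neuromuscular assessments before and after exercise (steps iii and vii) and the exercise session of about 45 minutes (step v) are separate steps. For the control: "CON will consist of repeating the aforementioned structure, replacing the exercise routine with 45 minutes of rest". Its purpose is "to provide a baseline reference for the hemodynamic and metabolic behavior of the sample over time".
- **PROCEDURES paragraph, Sessions 5-8.** The warm-up is 5 minutes of cycling, then "2 minutes of joint mobility, and performing 10 repetitions of each exercise at 70% of the load to be used in the session". Next: "After 2 minutes of recovery, baseline lactate will be recorded, and the speed of movement for each exercise will be recorded". CON is said to have the same content as the other sessions, "although warm-up processes, neuromuscular fatigue indicators, and exercise performance will not be conducted".

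Neither paragraph gives a total duration for CON, a fixed interval between the two resting recordings, or a statement that rest replaces the omitted warm-up, recovery or speed tests.

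**The concern.** The DESIGN paragraph replaces one step; the PROCEDURES paragraph removes several. A site cannot follow both to the letter. If it rests the participant for 45 minutes and also drops the warm-up and speed tests, the second recording starts earlier in CON than in 4S, 6S or 9S.

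CON is meant to show what pressure, autonomic indices and resting oxygen consumption do over time without exercise, so elapsed time is the feature it most needs to share with the exercise sessions. With a shorter interval, an exercise-minus-CON contrast at a given recovery minute also compares different times since arrival, since the first recording and since the last meal. Any spontaneous drift over the extra minutes would be counted as an effect of exercise.

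The Background criticises earlier studies for unequal recovery time and session duration, and the DESIGN paragraph equalises both across the three exercise sessions. The control session does not get the same treatment.

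**Working it through.** **1. What the 45 minutes covers.** Inputs from the DESIGN paragraph: four exercises; 9, 6 or 4 sets of 4, 6 or 9 repetitions; 45, 72 or 120 s between sets; 4 minutes between exercises.

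- Rest between sets, per exercise = (sets − 1) × rest: 8 × 45 = 5 × 72 = 3 × 120 = 360 s in all three sessions. Over four exercises: 24 min.
- Rest between exercises: 3 × 4 = 12 min. Total rest: 24 + 12 = 36 min.
- Repetitions: 4 × 36 = 144.
- Bout length = 36 min + 144 × seconds per repetition / 60. The repetition time is not stated, so 2 to 5 s is an assumption.

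| Assumed s per repetition | Bout (min) |
|---|---|
| 2 | 40.8 |
| 3 | 43.2 |
| 4 | 45.6 |
| 5 | 48.0 |

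The stated figure of about 45 minutes is reproduced by the bout alone. It leaves no room for a 10-minute warm-up.

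**2. The warm-up figure.** 5 min cycling + 2 min mobility + 40 repetitions at the same 2 to 5 s = 8.3 to 10.3 min, which agrees with the stated 10.

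**3. Nominal difference between sessions.** Steps common to all sessions (stiffness measurements, lactate samples, set-up of the recording) cancel from the difference.

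- 4S, 6S, 9S: 10 (warm-up) + 2 (recovery) + 45 (bout) = 57 min, plus speed tests and common steps.
- CON on the combined text: 45 min, plus common steps.
- Difference: 57 − 45 = 12 min, plus speed tests.

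**4. Allowing for the approximate bout.** Difference = 12 + bout − 45, before speed tests: 7.8 min at 40.8, 10.2 at 43.2, 12.6 at 45.6 and 15.0 at 48.0.

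**5. Speed tests.** Four exercises are tested before the bout, with no time given. The DESIGN list has a further test after the bout, which the PROCEDURES narrative does not place. Assuming 3 to 8 min before and 0 to 8 min after, the difference with a 45-minute bout is 12 + 3 + 0 = 15 to 12 + 8 + 8 = 28 min.

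**6. Which contrasts are touched.** Let d be the drift over the extra minutes.

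- Exercise minus CON: shifted by d.
- 4S, 6S and 9S against each other: warm-up and rest totals are equal, so d cancels.
- Condition-by-group interaction (the effect in Sample size justification): if d is the same in normotensive and hypertensive women, CON moves equally in both groups and d cancels. It remains only if drift differs by group.

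The document gives no drift rate, so d cannot be calculated from it.

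**The case against.** The best reply is that the shortfall is inferred. No sentence gives a CON total, and the phrases about repeating the structure and having the same content can be read as the same timeline with the active parts taken out. That reading is possible, but it is not written down. The only duration given for the replacement rest is the length of the bout.

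Several limits stand:

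- Twelve minutes is not a minimum. The bout length is approximate, and the 2-minute recovery is not named among the CON omissions. If it stays, the nominal difference is 10 minutes.
- The difference should not be given as a percentage of the interval, because the common steps inside that interval have no stated durations.
- Hypothesis 1 and most specific objectives compare set configurations, and the Background defines post-exercise hypotension as a fall below the pre-session level. Those comparisons do not depend on CON timing.

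Stronger readings are tempting, and the text does not support them:

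- *CON cannot serve as a time reference.* It keeps the pre-session recording, a rest period and the 60-minute second recording.
- *CON might include cycling and loaded repetitions.* A literal reading of the replacement sentence allows this, but the same paragraph says the control is without exercise.
- *The bias can be put in mmHg and set against the 3 mmHg in the Background.* That needs an assumed drift rate, and the 3 mmHg is a reduction after training programs, not a change after one session.
- *The powered interaction is biased.* A drift common to both groups cancels.

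**Conclusion.** The inconsistency is on the page and rests on no assumption. Taken together, the two paragraphs leave the CON interval between recordings nominally 12 minutes shorter than in the exercise sessions. The range is about 8 to 15 minutes at 2 to 5 s per repetition with the recovery dropped, and the untimed speed tests add to it. CON remains a valid no-exercise reference but is not matched on elapsed time. The result may be a small bias in exercise-versus-CON contrasts, whose size cannot be obtained from the document. Contrasts among 4S, 6S and 9S are unaffected, and the condition-by-group interaction is affected only if drift differs between groups. This is a cheap improvement, not a defect that undermines the design. It is best made before sessions start, because a visit cannot be re-timed afterwards.

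**What to change.** Reconcile the DESIGN and PROCEDURES paragraphs so that CON is described once. State that its warm-up, recovery and speed-test slots are kept as timed rest of the same length, so that the interval from the end of the first recording to the start of the second is the same in all four sessions. Log the actual start times of both recordings, so that any remaining difference can be seen and, if needed, allowed for in the analysis.

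The cost is a few lines of text and roughly 12 to 28 more minutes of rest in one visit per woman; the upper end depends on the assumed speed-test durations. No additional measurement is needed.

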# Abstract

Menopause causes hormonal changes that affect the acute and chronic physiological responses to exercise in postmenopausal women. In this regard, studies on cardiovascular responses to resistance exercise in women are scarce, making it particularly important to identify load parameters that modulate these adaptations. Previous studies by our research group have found that the set configuration influences the cardiovascular stress involved, although these results were obtained in young, healthy subjects. Therefore, the main objective of this project is to extend this line of research and analyze the effect of the set configuration on the cardiovascular responses of postmenopausal women. Additionally, since previous studies have shown that an individual's blood pressure level can influence the impact of resistance training programs on cardiovascular changes, we aim to compare these modifications in normotensive and hypertensive postmenopausal women. The project is designed to compare the effects of three training sessions with the same volume, intensity, duration, and work-rest ratio, but differentiated by set configuration. For this purpose, a sample of 60 postmenopausal women (30 normotensive and 30 hypertensive) will be recruited from local sports facilities to randomly perform three experimental sessions and one control session. Before and after each session, hemodynamic responses (systolic, diastolic, and mean blood pressure), cardiac performance (heart rate, cardiac output, and stroke volume among others), cardiac and vascular autonomic modulation (heart rate variability and blood pressure variability), baroreflex effectiveness (baroreflex sensitivity), neuromuscular fatigue, arterial stiffness, and metabolic responses (lactacidemia, resting metabolic rate using indirect calorimetry) will be evaluated. This analysis will identify set configurations with the highest and lowest cardiovascular stress. This project will provide useful information to optimize the prescription of resistance exercise in postmenopausal women, by identifying effort structures that potentially allow for both reducing cardiovascular stress and preserving physiological adaptations.

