Furthermore, it has been shown that improving strength through resistance training attenuates the hemodynamic response to handling absolute load magnitudes (30), suggesting it may have an effect on improving muscle performance and consequent reduction in cardiac demands during daily activities (18). Dynamic strength training also promotes vascular adaptations by improving vascular conductance and endothelial function, which could play a role in the blood pressure-reducing effect of this type of training (31). Despite this evidence, various meta-analyses addressing the impact of strength training on baseline BP levels agree on the need to deepen our understanding of this phenomenon due to the limited number of studies currently available, particularly regarding those conducted in hypertensive populations (12,27,29,31,32). For example, in the meta-analysis conducted by Cornelissen et al. (21), it was only possible to include 29 groups corresponding to dynamic resistance exercise programs, compared to the 105 groups considered for the analysis of aerobic exercise program effects. On the other hand, the effect of strength training in postmenopausal women has shown positive effects for BP reduction (33). However, as observed in the recent review by Loaiza-Betancur et al. (33), specific studies on cardiovascular adaptations to strength training in postmenopausal women are scarce, even more so in women with hypertensive conditions; most studies include sedentary women, and to date, only one study has investigated the effects of physical exercise in physically active postmenopausal women. This reflects a certain degree of uncertainty about adaptations to strength training in this specific population group, which, in principle, could also benefit from it.

A comprehensive evaluation of the cardiovascular effect of strength development programs requires considering both chronic adaptations and acute hemodynamic responses. In this regard, the phenomenon of Post-Exercise Hypotension (PEH), which is the decrease in BP to levels lower than those measured before the start of the session, has been observed following both aerobic activities and strength development routines, particularly in hypertensive populations (34–38). This makes physical exercise a valuable tool for the non-pharmacological control of hypertension (12–14).

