## Definition of study subjects

The sample will consist of postmenopausal women who are users of two facilities located in the influence area of the city of A Coruña: Termaria Casa del Agua (<https://termaria.es/>) and DOS Acea da Ma (<https://www.dosdeporte.es/inicio-acea-de-ama/>). As reflected in the PI's CV, both facilities have hosted some of the research group's transfer projects and have active agreements with the University of A Coruña. Additionally, the research group has contacted the company responsible for managing sports centers in the Oleiros area, near the Faculty where the present project will be carried out (Aqualia: <http://www.centrosdeportivosoleiros.es/oleiros/>) to recruit participants.

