## Selection and withdrawal of subjects

All participants in the sample will undergo a pre-participation medical consultation to assess potential absolute and relative contraindications for exercise and inclusion/exclusion criteria. This selection process will be supervised by [name] [name], a member of the research team and a specialist in Sports Medicine. The inclusion criteria will be as follows: for all women, having been postmenopausal for at least 5 years (counted after 12 consecutive months without menstruation), aged between 55 and 64 years, physically active (150-300 min/week of light-intensity or 75-150 min/week of moderate-to-vigorous-intensity exercise), having no more than 3 cardiovascular risk factors, being asymptomatic and without known cardiovascular, metabolic, or renal disease, and having a valid EU COVID certificate; for women with hypertension, in addition to the above, being diagnosed with well-controlled grade I hypertension with no more than one medication and low or moderate cardiovascular risk (*Hypertension*. 2020;75:1334-1357. DOI: 10.1161/HYPERTENSIONAHA.120.15026.). The exclusion criteria will be: having any other grade of hypertension, needing more than one medication to control hypertension or using any other medication that interferes with cardiovascular responses to exercise, being or having been on hormone replacement therapy, and presenting hypertensive response to exercise. Each participant must sign the corresponding Informed Consent Form (ICF), which will detail all the study characteristics and will follow the model suggested by the Galician Network of Research Ethics Committees (<https://acis.sergas.es/cartafol/05-Modelos-de-documentos>). As stated in the mentioned document, all participants will have the right to withdraw from the experiment if they wish to do so.

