## Statistical Analysis Plan

The statistical analysis will be carried out using the SPSS software version 27.0 (SPSS, IBM, Armonk, NY, USA) or different statistical packages (nparLD, lme4, rcompanion) for R (R software v4.1.2. R Foundation, Vienna, Austria). In addition to descriptive statistics, including measures of central tendency and dispersion, different inferential statistical procedures will be applied, selected appropriately based on the analyzed variables, design structure, or statistical properties of the variables. We highlight the main resources to be used:

- Factorial repeated measures ANOVA (2 factors of repeated measures, or repeated measures factor and between-subjects factor).
- ANCOVA with repeated measures, with baseline assessment as covariate.
- Mixed linear models, considering fixed and random effects. This procedure will also allow analysis in situations where some data may be missing.
- Linear correlation analysis.
- Linear and nonlinear regression analysis.
- Calculation of effect sizes: partial eta squared, Hedge's g, etc.
- Nonparametric statistics. In case of violation of assumptions of parametric procedures, even after variable transformation (e.g., logarithmic), alternative nonparametric procedures will be used. These include:
- Nonparametric ANOVA.
- Nonparametric correlation (Spearman).
- Nonparametric effect size: Rank Biserial Correlation).
- Friedman, Kruskall-Wallis, Wilcoxon, Mann-Whithney tests.

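### The pre-visit rule bars only intense activity, so active women may do light or moderate structured exercise shortly before the resting baseline; adding structured exercise to the 24-hour ban is a cheap, optional gain in precision

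*Protocol*

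**What the plan says.** The Protocol, Description of the intervention (PROCEDURES), asks participants to "avoid caffeine intake on the day of measurement and intense physical activity in the 24 hours preceding measurement". *Intense* is not defined there. In the same section the warm-up ride at 50-70% of estimated maximum heart rate is called moderate, so a private ride at that level would be allowed. The other preparation rules cover meals, caffeine and hydration. The 72-hour interval stands with the 12RM sessions and spaces study sessions, not the women's own training.

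On who takes part, Definition of study subjects says: "The sample will consist of postmenopausal women who are users of two facilities". Selection and withdrawal of subjects requires them to be "physically active (150-300 min/week of light-intensity or 75-150 min/week of moderate-to-vigorous-intensity exercise".

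On the mechanism, Background and Justification of the Project describes post-exercise hypotension, "which is the decrease in BP to levels lower than those measured before the start of the session", and says that it "has been observed following both aerobic activities and strength development routines, particularly in hypertensive populations".

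The Statistical Analysis Plan section lists several methods, one of which is "ANCOVA with repeated measures, with baseline assessment as covariate".

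**The concern.** The trial studies an after-effect of exercise, and one specific objective is to find the configuration that optimizes post-exercise hypotension. The reference is a 15-minute supine recording at the start of each of Sessions 5-8. A woman who has trained lightly or moderately beforehand may start from a lowered pressure at that visit and not at the others. Her pre-session value then varies for a reason unrelated to the study, and part of the fall that the session could produce may already have happened.

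At stake is some precision in the pre-post change, and a slightly understated raw fall. Pre-visit conditions are a protocol procedure, so this is not something a separate analysis plan would settle.

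**Working it through.** **1. The plan's own figure.** Sample size justification gives f = 0.12, correlation ρ = 0.75, m = 4 conditions, 2 groups, α = 0.05 and 80% power. For the within-between interaction, λ = f²·N·m/(1−ρ), with 3 and 3(N−2) degrees of freedom.
- N=50: λ = 0.0144×50×4/0.25 = 11.52, power 81.2%.
- N=48: power 79.4%, so the stated 50 reproduces.
- N=60 (planned): λ = 13.824, power 88.4%.

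**2. Assumptions, none of them in the protocol.** Systolic SD 12 mmHg (range 10-15); a bout before a share p = 0.20 of sessions (0.10-0.40); baseline lowered by d = 4 mmHg (3-5); a fraction k = 0.25 of that still present in the post recording (0-0.50); within-woman pre-post correlation r = 0.5 (0.3-0.7).

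**3. Size of the noise, central inputs.**
- Within-woman variance of a level: (1−0.75)×12² = 36.
- Variance of the pre-post change: 2×36×(1−0.5) = 36.
- Part due to outside exercise: p(1−p)·[d(1−k)]² = 0.16×3² = 1.44.
- Mean blunting of the raw fall: p·d·(1−k) = 0.2×4×0.75 = 0.6 mmHg (range 0.15-2.0), the same in expectation in all four sessions.

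**4. What a fully observed ban would gain.** Take 0.75, and so the variance of 36, as describing data collected under the current rule.
- *Change score:* the variance falls to 36−1.44 = 34.56, ratio 0.96. λ becomes 13.824/0.96 = 14.40 (N=60) and 11.52/0.96 = 12.00 (N=50). Power is 89.8% and 82.9%.
- *Baseline-adjusted ANCOVA:* removing the outside effect gives pre variance 36−0.16×16 = 33.44, post variance 36−0.16×1 = 35.84 and covariance 18−0.16×4 = 17.36. The residual is 35.84−17.36²/33.44 = 26.83, against 36×(1−0.25) = 27 now, ratio 0.9936. Power is 88.7% and 81.5%, a gain of 0.2 to 0.3 points.

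Taking 36 as the exercise-free variance and using the inverse ratio moves these four figures by at most about 0.1 point.

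**5. Range, same formulas.** Power with the ban, against 88.4% (N=60) and 81.2% (N=50) now:

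| Inputs | Change-score ratio | Change score, N=60 / N=50 | ANCOVA, N=60 / N=50 |
|---|---|---|---|
| Mildest: SD 15, p 0.1, d 3, k 0.5, r 0.5 | 1−0.2025/56.25 = 0.996 | 88.6% / 81.4% | 88.4% / 81.2% |
| Central, r 0.3 | 1−1.44/50.4 = 0.971 | 89.4% / 82.4% | 88.5% / 81.2% |
| Central, r 0.5 | 0.960 | 89.8% / 82.9% | 88.7% / 81.5% |
| Central, r 0.7 | 1−1.44/21.6 = 0.933 | 90.7% / 84.1% | 89.5% / 82.5% |
| Extreme: SD 10, p 0.4, d 5, k 0, r 0.5 | 1−6/25 = 0.760 | 95.7% / 91.2% | 91.9% / 85.7% |

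Adding r = 0.7 to the extreme row would make outside exercise 6/15 = 40% of the change variance. The change-score figures would then be 98.7% and 96.5%. That is a limit, not an estimate.

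**6. Bias.** Condition order is randomized and one rule precedes all four sessions, so nothing in the design makes a bout likelier before one condition than another. In a simulation at N=60 with change scores and no true effect (100,000 runs each), the interaction test rejected 4.9% of the time at central inputs. It rejected 5.0% with p = 0.4 and an outside effect of 5 mmHg in hypertensive and 3 mmHg in normotensive women. Mean shifts in between-session contrasts, and in their group differences, stayed below 0.02 mmHg.

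**The case against.** The best reply is that this is a preference. The protocol already standardizes meals, caffeine and intense activity. It randomizes order, takes a fresh baseline at each visit, includes a control session, lists a baseline covariate and plans 60 women where 50 are required. Every effect input above is assumed, and f = 0.12 is not tied to systolic pressure. The Background names aerobic and strength exercise, gives a direction only, and does not address light exercise. Rebooking is not free either: there are 60×4 = 240 visits, each with about 15+10+45+60 = 130 minutes of recording, warm-up and session. At the assumed 20%, some 48 visits (24-96 over the range) would need a changed routine or, if the rule were broken, a new date.

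Most of this stands. It rules out calling the current rule an error or a contradiction and keeps the point optional. It does not close the gap, because no other text restricts light or moderate exercise. The ANCOVA is one listed option, not a commitment.

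Two stronger readings are tempting.
- *The trial loses power, and falls below 80% at N=50.* If 0.75 described exercise-free data, λ would shrink by 36/37.44 = 0.962 and power would be 87.1% (N=60) and 79.5% (N=50). The protocol does not say that. The natural reading is data gathered under its own rules, so planned power stays at 88.4% and 81.2%, and a ban can only add to it.
- *The configuration or group comparisons are biased.* The common rule and randomized order do not support this, even if hypertensive women respond more strongly.

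**Conclusion.** The point holds as a cheap improvement of the lowest severity. The rule leaves light and moderate structured exercise before the baseline uncontrolled in a sample likely to do it, and the protocol's own rationale suggests that aerobic or strength exercise can lower pressure. The consequence is some avoidable within-woman noise and a raw fall blunted by about 0.6 mmHg under the central assumptions. The stated sample size and the planned comparisons remain valid.

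At central inputs the gain is about 1.4 points of power at N=60 and 1.7 at N=50 with change scores, and a few tenths of a point with ANCOVA. With r = 0.5 it runs from near zero to about 7 points (N=60) or 10 (N=50) for change scores. It depends on r: ANCOVA recovers most of the noise at central inputs with r up to 0.5, but less as r rises. Confidence in the direction is reasonable; the size cannot be derived from the protocol.

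**What to change.** Keep the existing ban and extend it, so that before each of Sessions 5-8, including the control session, participants avoid intense physical activity *and any structured resistance or aerobic exercise* in the preceding 24 hours. This should be an addition. Replacing the present wording would drop the ban on intense unstructured effort, such as heavy manual work.

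Ask about the last exercise bout at arrival, record the answer, and rebook where feasible if the rule was broken.

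Cost: one phrase in the protocol and one question per visit. Women would skip some habitual exercise before four visits, and an occasional visit of more than two hours would be rebooked.
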